### Surgical procedure

A stoma care nurse marks all stoma sites preoperatively. At the time of the stoma formation, randomisation to one of the three (or in applicable cases two) procedures is made. The centre point of the preoperatively marked place for the stoma is lifted and a circular skin incision is performed. Blunt or ‘semi-blunt’ dissection is used through the subcutaneous tissue, using a step-wise downwards movement with retractors assisted by sharp dissection as needed. When the ventral fascia of the rectus abdominis has been reached, dissection is stopped. A disposable, sterile measurement tape is used in the open surgical procedures, and the metric scale on the laparoscopic stapler is used in laparoscopic surgical procedures. The depth of the subcutaneous fat is measured. The width of the left colon together with its mesocolon is measured at the point where it will pass through the fascia (the depth of the subcutaneous fat + 20-30 mm). The fascia incision is calculated using this measurement - circular incision in the fascia with a diameter equalling 50% of the width of the patient’s left colon with mesocolon, or a cruciate incision where the arms measure one-half of the width of the patient’s left colon with mesocolon. If it is apparent that the incision will be too large, it may be reduced, but measured thoroughly and noted in the operative CRF. The muscular fibres are separated bluntly.

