Parastomal hernia is a long-term complication that is common; in the literature figures up to almost 50% have been reported [9,10]. There have been discussions regarding the placement of the stoma and effects on hernia incidence [11,12]; however, no studies have been sufficient in design or size to thoroughly answer the question. Attempts to reduce the rates of parastomal hernias have been made in the last few years with the placement of a mesh at the construction of the stoma [13-18]. However, these trials did not include studies of health-related QoL or health economic aspects. The placement of a prophylactic parastomal mesh has not been universally accepted, mainly due to a hesitance related to the possible risk of infection with a foreign body, but also as most studies were small in sample size [19]. Another suggestion for the basic construction of the stoma has been to make a circular instead of a cruciate incision in the fascia, but this has not been studied. It has been described in conjunction with the use of circular stapling devices, and no hernias were found, but the studies were small [20,21]. Thus, it is apparent that further studies are desired [17,22-24] and several randomised controlled trials are registered and ongoing.

The evaluation of parastomal hernias can be performed by clinical examination, CT scan or ultrasound [14,15,25,26]. All techniques have advantages and disadvantages, and the conclusion must be that evaluation of parastomal hernias may be difficult and must be standardised in a study.

The hypothesis to be tested in this study is that it is possible to obtain a lower incidence of parastomal hernia with a circular incision in the abdominal fascia or with reinforcement with a mesh instead of a cruciate incision in the abdominal fascia.

The study will provide a precise control compared to the two interventions with thorough measurements of the bowel and the trephine opening to improve the evaluation of the surgical technique. It will also enable an evaluation of QoL and health economy.

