### Randomisation

All participating patients give written informed consent. After inclusion no changes are made in the planning for the operation. The patient will be randomised to one of the three groups of intervention during surgery in the operating theatre directly prior to the stoma formation (Figure 1). Randomisation will be performed by blocks of closed envelope systems in each participating hospital. It will be balanced and stratified by hospital. Laparoscopic as well as open procedures will be included and, although not stratified by open or laparoscopic procedures, their use will be noted in the CRF.

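### As the steps are described, the arm is allocated before the bowel width that sets the fascial opening is measured; measuring first would avoid this

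*Protocol article*

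**What the plan says.** The Randomisation section states that patients are "randomised to one of the three groups of intervention during surgery in the operating theatre directly prior to the stoma formation", using envelopes in blocks at each hospital. The Surgical procedure section repeats the timing: "At the time of the stoma formation, randomisation to one of the three (or in applicable cases two) procedures is made". It then describes, in turn:

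- the skin incision: "The centre point of the preoperatively marked place for the stoma is lifted and a circular skin incision is performed";
- dissection down to the ventral rectus fascia, where it stops;
- the first measurement: "The depth of the subcutaneous fat is measured";
- the second measurement: "The width of the left colon together with its mesocolon is measured at the point where it will pass through the fascia";
- the sizing step: "The fascia incision is calculated using this measurement", with the circle's diameter or the arms of the cross set at half the measured width.

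Two departures from the calculated size are allowed. Before the cut, "If it is apparent that the incision will be too large, it may be reduced, but measured thoroughly and noted in the operative CRF". Afterwards, the two stoma formation subsections (with and without mesh) call for widening where the opening proves insufficient, again measured and recorded.

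The Data collecting and monitoring section has the surgeon complete the operative CRF, which holds these measurements. The Follow-up section acknowledges that the study is not blinded. The Background presents the measurements as a strength of the trial, promising "thorough measurements of the bowel and the trephine opening to improve the evaluation of the surgical technique".

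**The concern.** The trial compares incision shape and mesh reinforcement while holding the opening to a common rule based on each patient's own bowel. That rule is only as neutral as the width fed into it. The width is read with a tape or a stapler scale on soft tissue that includes mesocolon, so it leaves some room for judgement. If the reader knows which construction comes next, the reading could differ by arm without anyone intending it. Opening size would then differ systematically between arms and be mixed with the effect of shape or mesh.

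Two further uses of the width depend on it. Any reduction or widening can be judged only against the recorded width, so a width taken with the arm known is a weaker reference. The closing paragraph of the Statistical analysis section also allows exploratory regression on patient characteristics and perioperative factors, for which bowel width is a natural candidate. Measured after allocation, it may itself have been affected by the arm and cannot safely be treated as a baseline variable.

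**Working it through.** The plan gives no figure on this point to reproduce, so the check is of sequence and dependence.

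**1. Where allocation falls.** The Randomisation section puts it immediately before stoma formation. The Surgical procedure section puts it ahead of the skin incision. The measurements are described as part of forming the stoma. The two sections therefore agree, and both place allocation before measurement.

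**2. When the arm is first needed.** Taking the described steps in turn:

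- skin incision: same in all arms;
- dissection to the fascia: same in all arms;
- fat depth: same in all arms;
- colon-with-mesocolon width: same in all arms (the mesh subsection refers back to these measurements);
- fascial incision: circular or cruciate, so the arm must be known here.

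Nothing before the fascial incision requires the allocation.

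**3. How an error in width would carry through.** Let W be the true width and e the relative error in reading it. The target (circle diameter or cross arm) is 0.5 × W. With the error it is 0.5 × W × (1 + e). The ratio is 1 + e, so a relative error in width passes one-for-one into the target in every arm. The document gives no measurement error and no expected difference in e between arms. Without these, and without a link from opening size to herniation, no bias in the hernia rate can be calculated.

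**4. What measuring first would protect.**

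- Recorded width: yes.
- Calculated target: yes, because it follows from the width by a fixed rule.
- Reduction judged necessary before the cut: no, since it concerns the incision the surgeon is about to make, knowing the arm.
- Later widening: no, since it follows the cut.

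**5. What depends on it in the planned analysis.** Yes/no outcomes, which include the primary endpoint, are compared by chi-square tests without width as a covariate. The 62 patients per group before drop-out, the 80 recruited per group and the significance level do not involve width. Only the optional exploratory regression could use it.

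**The case against.** The strongest reply is that nothing here is misstated. Randomising in theatre just before the stoma is formed is already late allocation, and asking for it a few minutes later is a preference. The opening words of the randomisation sentence can be read as a general time marker. No sentence says that the envelope must be opened before the tape is applied, and none says who holds the tape. The article condenses a fuller protocol, and the CRF or site instructions may already put measurement first. There are also safeguards: a defined instrument, a defined point on the bowel, one sizing rule for all arms, and a duty to measure and record every departure from it.

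Most of this stands. The order is an inference, and the safeguards narrow the risk. They do not remove it: recording departures shows how the final opening differs from the target, but does not show whether the width behind the target was read neutrally. The article also does more than leave the order open, because the sequence it describes is the weaker one.

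Three stronger readings are not supported:

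- A reader might infer that measurement is biased in this trial. The document offers no evidence of that, nor a direction in which it would run.
- A reader might square the width error to obtain a difference in circular area between arms. Only one arm has a circular incision; control and mesh both use a cruciate one, so that contrast does not exist here. Any percentage chosen for the error would also be unsourced.
- A reader might infer that the primary analysis is compromised because width is not a true baseline covariate. No planned primary analysis uses it.

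**Conclusion.** The point holds as a minor, avoidable weakness in the described order of steps. As written, the unblinded surgeon may know the arm while measuring the width from which the fascial opening is calculated, in a trial that relies on those measurements to standardise technique. It is neither an error nor a contradiction.

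Its size is unknown. The conclusion rests on reading the order of sentences as the order of events. If sites already measure first, the sponsor need only say so. The benefit of changing the order assumes that the surgeon cannot predict the next allocation from earlier envelopes at that hospital.

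**What to change.** In the Randomisation and Surgical procedure sections, state that subcutaneous fat depth and colon-with-mesocolon width are measured and written in the operative CRF before the envelope is opened, and instruct sites accordingly. No sizing rule, technique or clinical judgement changes.

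Width then becomes a true pre-randomisation variable for the exploratory regression. The Trial status section reports that recruitment is under way, so this applies only to patients enrolled after the change. The date of the change at each site should be kept so that earlier widths are not assumed to be baseline values.

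Reductions and widenings remain unblinded. Their frequency and size, and the final opening relative to the recorded width, should be compared between arms from the CRF.

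The cost is a reordered sentence in two sections and a site instruction. The downside is that the envelope is opened a few minutes later, with the skin incision already made.

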#### Stoma formation without a mesh

The dorsal fascia is opened. The proximal colon end is taken through the stoma incision (plica epiploicae may be removed, if necessary). Care is taken to ensure adequate circulation to the colon involved in the stoma. If the width of the incision is insufficient for adequate circulation, a widening should be performed, measured and noted in the CRF. The muco-cutaneous suturing is made using 4-0 absorbable interrupted sutures, three-point sutures (mucosa, muscular layer and skin) starting with one in each quadrant and adding ordinary muco-cutaneous sutures in between as needed. The height of the stoma after it is created should be at least 1 cm.

#### Stoma formation with a mesh

The incision in the fascia is performed with a cruciate incision, with size according to the measurements described above, and the mesh will be placed using the sublay technique as previously described [14]. A fine-thread, large-pore lightweight polypropylene monofilament mesh measuring 10 × 10 cm is used. The mesh is placed dorsal to the rectus abdominis muscle and anterior to the posterior rectus fascia by dissection through either midline in open surgery or by blunt dissection under the rectus abdominis muscle in laparoscopic surgery. A cruciate incision with a size measured according to the instructions above is made in the anterior sheath of the fascia and in the mesh. The bowel is brought out through a cross-cut in the centre of the mesh where the arms should measure one-half of the width of the patient’s left colon and its mesocolon. If the width of the incision is not sufficient, a widening should be performed, measured and noted in the CRF. Stitches fix the lateral corners of the mesh to the posterior rectus sheath. The medial corners of the mesh are grasped with a stitch of the running suture closing the midline incision during open surgery, and this is not applicable to laparoscopic procedures.

The diameter of the stoma is measured immediately after the operation.

### Postoperative treatment

Local guidelines are followed and must be applied equally in all three (in applicable cases, two) groups, without any systematic differences. Any postoperative treatment with antibiotics must be noted in the CRF, including reasons and total treatment time. This applies to both systemic as well as oral antibiotics. All postoperative information regarding stoma and stoma function will be given according to local routines.

### Follow-up

The follow-up during the postoperative hospital stay is recorded in a CRF. Time until full oral feeding is resumed and time until first gas and stool are registered.

Patients will be clinically examined at 6 (5–7) months and at 12 (11–13) months postoperatively and further as needed (suspected parastomal herniation), by a surgeon (not one of the colorectal team) preferably specialised in hernia surgery, to diagnose a possible parastomal hernia. At 12 months patients for whom no clinical parastomal herniation has been found will undergo a CT examination of the abdomen (wall), performed in prone position [25], which also will be part of the routine 12 months follow-up by abdomen CT for colorectal cancer patients. A study-specific standardised referral to abdomen CT is used, and although the study is not blinded, no information as to type of stoma construction is included. All radiologic departments use a specific protocol for this part of the abdomen CT.

Stoma height, diameter, colour, skin irritation and bandaging problems are documented by nurses specialised in stoma care during hospitalisation and at 4-6 weeks, 6 months and 12 months and are registered in a CRF.

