### Endpoints

The primary endpoint is the presence of parastomal hernia as detected by clinical examination or CT scan at 12 months after surgery. A bulge in the vicinity of the stoma is not sufficient in this study to define a parastomal hernia. If there is any doubt in the clinical setting, the patients must be examined by a CT scan in a prone position. Secondary endpoints include: re-admission rate, postoperative complications (classified according to Clavien-Dindo [27]), stoma-related complications (registered in the case record form (CRF) at Stoma Care nurse follow-up), total length of hospital stay during 12 months, health-related quality of life and health economic analysis, re-operation rate, mortality within 30 days and 12 months of primary surgery. Re-admissions and re-operations as registered in the hospitals’ databases at 24 months to ascertain that possible long-term complications related to the stoma construction are identified.

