### Statistical analysis

The Swedish trial on the effect of prophylactic net placement has reported 50% incidence of parastomal hernia without mesh [14]. Our own data on abdominoperineal excision from Sahlgrenska University Hospital indicate an incidence of 25% [28]. The power calculation based on available information has used the hypothesis that the cruciate incisional stoma formation, performed as described here, should result in parastomal hernia incidence of 30% and the circular incision or prophylactic mesh reinforcement could reduce this incidence to 10% each. An 80% power and a 5% level of significance with a two-sided alternative hypothesis would require 62 patients per group using a chi-square test. Expecting 20% drop-outs, 80 patients will be recruited in each group.

The primary analysis will be based on the full analysis set. This analysis set is designed to be consistent with recommendations set forth in International Conference on Harmonisation (ICH) guidance document E9: Statistical Principles for Clinical Trials, and is intended to adhere as closely as practically possible to the intention-to-treat (ITT) principle. The full analysis set will consist of all randomised patients who had surgery and who contributed with any follow-up data.

Patients will be analysed according to randomised procedure. A sensitivity analysis evaluating the actual procedure will be made for the most important outcomes.

All hypothesis testing will be conducted using two-sided tests, and P values ≤ 0.05 after rounding will be considered statistically significant. A pair-wise comparison between the experimental arms and the control arm will be performed and the significance level will be corrected using the Bonferroni-Holm method. Event-type variables (yes or no) will be compared between randomised procedures using chi-square tests, and relative risks and risk differences will be estimated. Where appropriate, the time to event will be described using Kaplan-Meier plots. The number of events of a certain type (for example, number of complications or re-operations) will be analysed using Poisson regression with randomised procedure as a factor and time under observation as an offset variable.

Total length of hospital stay will be compared between groups using Wilcoxon’s rank-sum test. Sub-group analyses specifically looking at the following groups of patients will be performed:

a) BMI >30 kg/m2

b) Immunosuppression

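### Nothing in the protocol keeps the examining surgeon unaware of allocation, and a clinical hernia diagnosis made without doubt counts as a primary event with no required CT

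*Protocol article*

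**What the plan says.** All references are to the protocol article.

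- **Endpoints.** "The primary endpoint is the presence of parastomal hernia as detected by clinical examination or CT scan at 12 months after surgery". Two rules restrain the clinical route: "A bulge in the vicinity of the stoma is not sufficient in this study to define a parastomal hernia", and "If there is any doubt in the clinical setting, the patients must be examined by a CT scan in a prone position".
- **Follow-up, examiner.** Patients are examined at 6 and 12 months, and in between if a hernia is suspected, "by a surgeon (not one of the colorectal team) preferably specialised in hernia surgery, to diagnose a possible parastomal hernia". No masking of this surgeon is stated.
- **Follow-up, CT.** "At 12 months patients for whom no clinical parastomal herniation has been found will undergo a CT examination of the abdomen (wall", in prone position. On the CT referral, "although the study is not blinded, no information as to type of stoma construction is included".
- **Background.** The authors conclude that "evaluation of parastomal hernias may be difficult and must be standardised in a study".
- **Statistical analysis.** The planned sensitivity analyses concern the procedure actually performed and the centres that allocated both treatments.

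**The concern.** The two routes to a primary event are not checked alike. A clinical negative at 12 months is followed by CT, so a missed hernia has a second chance of being found. A clinical positive about which the examiner has no doubt becomes an event at once, and no CT is required that could overturn it.

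In an unblinded study, the person making that call may know which construction the patient received. The stated hypothesis is that a circular incision or a mesh gives fewer hernias than a cruciate incision. An examiner who shares that expectation and knows the arm could call a hernia more readily in control patients. Those extra events would go straight into the primary comparison, in the direction of the hypothesis.

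Masking looks feasible. The examiner is not from the operating specialty, all arms share a circular skin incision, and the features that differ (the shape of the fascial opening, and a mesh behind the rectus muscle) lie beneath the skin.

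**Working it through.** **Step 1. What happens to each clinical verdict at 12 months**

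| Clinical verdict | Next step in the protocol | Can an error be corrected? |
|---|---|---|
| No hernia | Study CT; referral omits stoma type | Yes, by CT |
| In doubt | Prone CT required | Yes, by CT |
| Hernia, no doubt | Counts as an event; no CT required | No |

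The exposure is the last row only: false positives held without doubt.

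**Step 2. The plan's own figure**

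Inputs from Statistical analysis: 30% versus 10%, two-sided 5% level, 80% power, chi-square test. With pooled variance and no continuity correction, the mean rate is 0.20 and

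n = [1.960 × √(2 × 0.20 × 0.80) + 0.842 × √(0.30 × 0.70 + 0.10 × 0.90)]² / 0.20² = (1.109 + 0.461)² / 0.04 ≈ 61.6, so 62 per group.

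This matches the stated 62. Recruiting 80 with 20% drop-out leaves 80 × 0.80 = 64 evaluable per arm, the number used below. The power calculation is not in question.

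**Step 3. Illustrative size (assumed error rates)**

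Let p be the true rate, equal in both arms. Let f be the share of hernia-free control patients wrongly called positive without doubt, so that f is what remains after the doubt rule. Assume no such errors in the experimental arm and correct classification of everyone else. Then

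- observed control rate = p + (1 − p) × f
- spurious difference = (1 − p) × f

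At p = 20%, 0.80 × 0.05 = 0.04 and 0.80 × 0.10 = 0.08. In patients, 64 × 0.80 = 51.2 are hernia-free, so this means about 2.6 or 5.1 wrongly classified control patients.

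The table gives the spurious difference and the chance of a significant result favouring the experimental arm. That chance should be 2.5%. It is computed by the two-proportion normal approximation with 64 per arm, at the 5% level for one comparison, before the Bonferroni-Holm correction.

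| True rate, both arms | f = 2% | f = 5% | f = 10% |
|---|---|---|---|
| 10% | 1.8 points; 5.1% | 4.5 points; 11.8% | 9.0 points; 30.2% |
| 20% | 1.6 points; 4.1% | 4.0 points; 7.8% | 8.0 points; 18.3% |
| 30% | 1.4 points; 3.7% | 3.5 points; 6.2% | 7.0 points; 13.0% |

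**Step 4. Other patterns of error**

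Under the planned 30% versus 10%, power with 64 per arm is 81.5%.

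- A 5% false-positive rate in both arms gives 33.5% versus 14.5% and 71.6% power.
- A 5% rate in the experimental arm only gives 30% versus 14.5% and 56.0% power.

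The damage therefore depends on a pattern of error that the documents do not describe.

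**The case against.** The endpoint definition already answers much of this. A bulge alone does not count, and any doubtful case must have CT. The examiner is independent of the operating specialty and preferably a hernia specialist. Missed hernias are largely recovered by CT. What is left is a false positive that goes beyond a bulge, is held without doubt, and is more frequent in the cruciate arm. Nothing in the documents shows that this occurs, or in which direction. The article is also a condensed account, and an instruction on what the examiner may see could stand in the full protocol.

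Most of this stands as a limit on the point, but it does not remove it:

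- The doubt rule depends on the examiner's own sense of doubt, which knowledge of the arm can influence.
- Coming from another team makes knowledge of the allocation less likely, but it does not rule it out.
- The article does not pass over masking in silence. It calls the study not blinded and names the one place where the technique is withheld, so the criticism is of a stated choice. If the full protocol already withholds the allocation from the examiner, only that sentence needs correcting.

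Three stronger readings are not supported:

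- **That clinical positives are never checked.** Doubtful ones must go to CT.
- **That half of the endpoint is affected.** The clinical route is one of two, and no split of events by route is given.
- **That the CT route is masked.** Only the referral is said to omit the stoma type. The radiologist is not described as unaware of allocation.

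**Conclusion.** The point holds as a limited weakness in how the primary endpoint is ascertained. A clinical diagnosis made without doubt, by a surgeon who is not stated to be unaware of allocation, is an event with no required CT, whereas clinical negatives are followed by CT. One diagnostic route is therefore open to differential false positives.

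The size cannot be derived from the documents. On assumed extra false-positive rates of 5% to 10% in hernia-free control patients only, with a true rate of 20% in both arms, the spurious difference is 4 to 8 points. The chance of a falsely favourable result then rises from 2.5% to between 7.8% and 18.3%. Over the wider grid of true rates of 10% to 30% and error rates of 2% to 10%, the difference is 1.4 to 9.0 points and the chance is 3.7% to 30.2%. None of these cases reaches the planned 20 points. A reader should not infer that bias is shown to be present, or that the sample size is wrong.

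**What to change.** **Main change.** Add to the follow-up instructions that the examining surgeon is not told the allocation, and does not see the operative CRF or operation note, before recording the hernia verdict. This should apply to the 6-month, 12-month and any additional examinations. Add one CRF item recording whether the examiner knew the allocation at that time.

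**Cost.** One instruction and one tick-box, with no extra staff, visits or scans. Patients or records will sometimes reveal the arm. The CRF item shows how often this happened and whether it differed by arm.

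**Optional.** Report hernias by diagnostic route in each arm. Where a clinically positive patient has the routine 12-month cancer CT anyway, its reading can be given as supportive evidence. It should not become a confirmed-hernia endpoint: the routine scan is mentioned only for colorectal cancer patients, while eligibility covers any elective colostomy, and it is not stated to be prone in clinical positives.
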